## Abstract

**Background:**

Although rates of preterm birth continue to increase globally, identification of preterm from low birth weight infants remains a challenge. The burden of low birth weight vs preterm is greatest in resource-limited settings, where gestational age (GA) prior to delivery is frequently not known because ultrasound in early pregnancy is not available and estimates of the date of the mother’s last menstrual period (LMP) may not be reliable. An alternative option is to assess GA at birth to optimize referral and care of preterm newborns. We previously developed and pilot-tested a system to measure the simplified gestational age score (SGAS) based on 4 easily observable neonatal characteristics.

**Objective:**

The objective of this study is to adapt the scoring system as a tablet app (potentially scalable approach) to assess feasibility of use and to validate whether the scoring system accurately predicts prematurity by itself, over and above birth weight in a large sample of newborns.

**Methods:**

The study is based in Nagpur, India, at the Research Unit of the National Institute of Child Health and Human Development’s Global Network for Women’s and Children’s Health Research. The Android tablet app for the SGAS (T-SGAS) displays de-identified photographs of skin, breasts, and genitalia across a range of GAs and line drawings of infant posture. Each item is associated with a score. The user is trained to choose the photograph or line drawing that most closely matches the newborn being evaluated, and the app determines the neonate’s GA category (preterm or term) from the cumulative score. The validation study will be conducted in 3 second level care facilities (most deliveries in India occur in hospitals, and women known to be at risk of preterm birth are referred to second level care facilities). Within 24 hours of delivery, women and their babies who are stable will be enrolled in the study. Two auxiliary nurse midwives (ANMs) blinded to prior GA assessments will use the T-SGAS to estimate the GA status of the newborn. An independent data collector will abstract the GA from the ultrasound recorded in the hospital chart and record the date of the mother’s LMP. Eligibility for analysis is determined by the ultrasound and LMP data being collected within 1 week of each other to have a rigorous assessment of true GA.

**Results:**

Publication of the results of the study is anticipated in 2019.

**Conclusions:**

Until GA dating by ultrasound is universally available and easy to use in resource-limited settings, and where there are restrictions on ultrasound use due to their use for sex determination and abortion of female fetuses, this study will determine whether the T-SGAS app can accurately assess GA in risk categories at birth.

**Trial Registration:**

ClinicalTrials.gov NCT02408783; https://clinicaltrials.gov/ct2/show/NCT02408783 (Archived by Webcite at http://www.webcitation.org/75S2kmr3T)

**International Registered Report Identifier (IRRID):**

DERR1-10.2196/11913

## Introduction

An estimated 15 million children per year (11% of live births) are born prematurely (less than 37 weeks of gestation), predominantly in Africa and Asia [1]. Prematurity rates are increasing globally and of concern because prematurity is a well-recognized risk factor for increased neonatal mortality and morbidity [2-4]. In settings where the incidence and adverse consequences of prematurity are the highest (ie, resource-limited settings), pregnant women may not know the date of their last menstrual period (LMP) and ultrasound is often not available—particularly first-trimester ultrasound, when estimates of gestational age (GA) are more accurate [5]. Since premature birth may not be anticipated by health care providers prior to labor and delivery [6,7], it is important that prematurity be identified at birth so that preterm neonates receive effective interventions as soon as possible after delivery [8].

When prenatal GA is unavailable, it can be estimated at birth by physical examination of the newborn using scoring systems such as the 12-item New Ballard Score (NBS) [9] and the 22-item Dubowitz score (DWS) [10]. A simplified 11-item scoring system adapted from the NBS was developed by Meharban Singh in 1975 and is in use in India [11]. However, even the use of simplified GA scoring systems in first (Primary Health Centers) and second (district and regional healthcare centers) level facilities in resource-limited settings, where the majority of the world’s neonates are born, is difficult. Further, predicted GA from these scores has often been compared with women’s reports of their LMP, and is not a reliable gold standard, such as first trimester ultrasound [12]. In addition, these scoring systems have not been adequately evaluated for regional, geographical, racial or ethnic robustness. A pragmatic postnatal GA assessment tool that can be used by community birth attendants or auxiliary nurse midwives (ANMs) who deliver the majority of newborns in rural health settings is urgently needed to optimize referral and care of preterm neonates when prenatal GA is unavailable.

We previously used the NBS, DWS and Meharban Singh scoring system to develop a 4-item simplified gestational age score (SGAS) for use in low birth weight newborns in India [13]. The 4-item scoring system is as follows: posture (0 to 4), skin (–1 to 5), breasts (–1 to 4), and genitals (–1 to 4). The total score was used to define 4 SGAS categories: <32 weeks, ≥32 to <35 weeks, ≥35 to <37 weeks, and ≥37 weeks. The SGAS then underwent initial testing in 171 newborns [13] and was found to have a high positive predictive value for very preterm (<32 weeks gestation) and moderate preterm (32-35 weeks gestation) neonates compared with the NBS. In our prior study, a score of <14 predicted that a newborn was preterm (GA of <37 weeks). Agreement between independent raters for the SGAS was higher than that for the NBS (Cohen’s kappa 0.83 and 0.71, respectively) indicating that the SGAS was promising to assist with community-based triage and referral decisions for preterm neonates, but in need of further validation.

We elected to conduct a validation study after adapting the SGAS scoring system as a mobile health (mHealth) intervention for two reasons. First, the items used for the SGAS were derived from the NBS and the scoring is based on a description of the skin, breasts, and genitalia that require appropriate training when used by community health workers (such as ANMs) [14]. We proposed that it would be easier to train first level facility health care workers to estimate the score for each item if there was a photograph as well as a text description of the item. Second, since providing a standardized photograph for comparison would be easier using an mHealth app and, given the widespread availability and use of mobile phones, and even tablets, in resource-limited settings [15], this approach would be novel and potentially feasible. As recently reviewed by McBride et al [16], mHealth is increasingly being accepted by community health workers to improve knowledge about maternal and child health [17] and access to care [18], but there are few studies that have used mHealth apps to guide need for referral of neonates to second level care facilities. In this paper, we describe the development of a pictorial-based tablet app for the SGAS (T-SGAS) and its use as an assessment tool. The T-SGAS will be evaluated by ANMs, who are the frontline skilled birth attendants, particularly in first and second level care facilities in most of India, to assess GA compared with ultrasounds obtained as early as possible during pregnancy.

The Eunice Kennedy Shriver National Institute of Child Health and Human Development’s (NICHD’s) Global Network for Women’s and Children’s Health Research is a partnership and collaboration between 7 multidisciplinary research units and a Data Coordinating Center dedicated to improving maternal and child health outcomes and building health research capacity in resource-limited settings. Goals include testing feasible, cost-effective, sustainable interventions to provide guidance for the practice of evidence-based medicine. The research unit in Nagpur, India and the Data Coordinating Center at RTI International developed and will help validate the T-SGAS.

The objective of this paper is to describe the development of the T-SGAS, its preliminary assessment of feasibility, and a protocol to evaluate whether it accurately predicts prematurity in a large sample of newborns. The programmatic feasibility of using the app will be evaluated by assessing the agreement of GA assessments performed by 2 ANMs. The accuracy of the app will be assessed by comparing the assessment of preterm vs term-based newborns on LMP alone, ultrasound alone, and the combination of LMP and ultrasound.

## Methods

### Development of the Tablet App for the SGAS (T-SGAS)

The development of the T-SGAS was achieved through the following steps: (1) collection of a repository of photographs of the items in the SGAS for preterm and term newborns; (2) selection of photographs for the range of scores for skin, breasts, and genitalia and consensus of neonatology experts for the best photograph of each item score; and (3) development of the Android T-SGAS for visually matching the newborn to the photographs, which auto-calculates the total SGAS and assigns a GA after the user choses the appropriate photograph. A score of <14 is considered to represent preterm, as we had found in our prior study [13].

De-identified photographs of skin texture, breasts, and genitalia of 1800 newborns of varying GA within 24 hours of birth were obtained from five tertiary care hospitals in Nagpur, India, after obtaining written informed consent from the mother of the neonate. A panel of three senior neonatologists, trained in the use of the NBS, selected photographs that best matched the original text description of the development of the skin, breasts, and genitalia [9] based on agreement of at least two of the neonatologists. Since the goal was to select the most unambiguous pictures, whenever possible, we chose pictures selected by all three neonatologists to match each description. The neonatologists did not use the score to make their selection—the score was automatically assigned based on the text and picture description. The three neonatologists selected and matched the photographs together (not independently and not blinded to the interpretation of the other neonatologists). If more than one photograph matched an item and score, the photograph with the best clarity, lighting, and detail was selected. Posture was depicted by line diagrams instead of using photographs of newborns that could be identified. The 25 images selected by the neonatologists (7 photographs of the skin, 6 of the breasts, 6 of the male genitalia, and 6 of the female genitalia) and the line diagrams of posture with their descriptions were embedded in the T-SGAS (see Figure 1). Note that the scoring range from –1 to +5 was based on the original Ballard Scoring System [9] and retained in the NBS System. For example, skin ranged from –1 to +5, breast and male and female genitalia ranged from –1 to +4, and pictures of posture ranged from 0 to +4. This is why there are 5 empty slots in Figure 1. Each item has an associated score. The T-SGAS then auto-calculated the total score and classified the newborn’s GA. The conversion of T-SGAS to GA categories is shown in Table 1.

The T-SGAS was designed to collect data in 5 different forms using the same tablet (forms SGAS01-SGAS05). Forms SGAS01 and SGAS02 were used by ANM-1 and ANM-2 to assess GA, blinded to each other’s assessment. Form SGAS03 contained data on demographic details of the mother and the newborn, foot length of the newborn, GA based on LMP, and GA based on the earliest ultrasound in pregnancy to determine study eligibility. Form SGAS04 was a random sample verification form for quality assurance by the master trainers to assess the GA, as well as to verify the details from the source documents. Form SGAS05 recorded any protocol deviations or unexpected events in the course of the neonate’s enrollment.

The T-SGAS was written in Java and was developed using the Eclipse platform to run on Android-based tablets, as a cost-effective and easy-to-use app that includes support for multiple-languages, enables field data collection in low- and middle-income countries, and has capabilities to integrate diverse data management methodologies. We would also consider developing a version of the T-SGAS for iOS should there be interest from potential users. The software was developed as a suite of software tools for form design, implementation, and reporting. Various data management models were developed to work in diverse conditions including: SIM based tablet or Wi-Fi transmission with Dropbox/Dropsync integration, File Transfer Protocol (FTP), migration of data over SD cards or USB cables and use of Wi-Fi capable external drives. Confidentiality of the data was ensured through encryption of the data on the tablet and during upload to Dropbox or the FTP site. Access to the data are limited to a few personnel who work on the server, which is behind a firewall. The T-SGAS was tested frequently during development for usability and reliability on SIM card–enabled Android tablets. The final T-SGAS was secured by user-specific passwords.

Built-in validations and range checks were implemented as needed on questions to prevent users from moving to the next question on the form if the validation failed. Examples of system-checks and automation include:

Based on the eligibility questions on the first data collection form (SGAS01), the T-SGAS automatically generated the rest of the forms for potentially eligible subjects (although the potential accuracy of GA was not known at this stage).Based on gender (male or female) the app presented the 3 neonatal characteristics with the correct gender assignment as the fourth neonatal characteristic.Cross form checks were also programmed for questions (such as the current status of the baby, sex of the baby, etc).To reduce errors, key fields from the enrollment form SGAS01 (such as date and time of delivery, consent obtained, etc), were also programmed to be present on the introduction screens of forms SGAS02 to SGAS05, which recorded the results of the actual GA assessment.

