The tablet-based forms are password protected and accessible only by using log-in credentials. After log-in, a Case Management Screen appears with the list of facilities and a preinstalled drop-down menu of identification numbers (IDs). The first ANM (ANM-1) sequentially allocates the IDs to the women who consented and delivered singleton live births. ANM-1 evaluates the newborn and uses her log-in credentials to open the electronic study form (SGAS01) that records date and time of delivery, gender of neonate, consent status, and then uses the touch screen to choose pictures that most accurately represent the neonate’s skin, breasts, genitals, and posture (Figure 2). The GA score is then auto-calculated and the neonate is classified into a specific GA group. On completion of the form, a pop-up warning message appears on the screen to verify the assessment and form entries. When verified, the form is saved and cannot be reopened by ANM-1. Completion of the form enables automatic population of subsequent forms with the same ID for the same participant. Color coding is used to identify the pending forms, so that ANM-2 can assess the same newborn using her log-in credentials within 24 hours of birth (using form SGAS02).

Inclusion and exclusion criteria to participate in the tablet app for the simplified gestational age scoring system (T-SGAS) study.Inclusion criteriaMother had regular menstrual cycles prior to pregnancyMother knew the date of her last menstrual periodMother has a report of at least one prenatal ultrasound assessment of gestational age during pregnancy (ideally in the first trimester)Mother and baby are clinically stableMother delivered singleton neonate at the study hospitalNeonate is within the first 24 hours of lifeExclusion criteriaNeonates with birth asphyxia or who were resuscitatedNeonates with major congenital anomalies or signs of neurological depression

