### Analysis

#### Sample Size

We have assumed that the prevalence of preterm births will be approximately 10% in this population. In a 2-sided test for sensitivity, a sample size of 7440 will achieve 80% power at a significance level of 0.05 when the sensitivity under the null hypothesis is 0.60 and the sensitivity under the alternative hypothesis is 0.65. This sample size will also be sufficient to achieve 80% power at a 0.05 significance level in a 2-sided test for specificity, when the specificity under the null hypothesis is 0.70 and the specificity under the alternative hypothesis is 0.75, which requires a minimum of 704 subjects.

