#### Analysis plan

Firstly, we will use the Fleiss kappa statistic to estimate agreement between GA (as a dichotomous outcome) measured by ANM-1 and ANM-2. Since our goal is to evaluate the use of the T-SGAS by ANMs, we will not determine which AMN is “correct” (eg, by having a third AMN independently assess the GA of the baby to resolve disagreement). Instead, we will assess the screening accuracy (sensitivity, specificity, prevalence of preterm) of the T-SGAS for both ANMs using 4 different reference standards: LMP alone, ultrasound alone, either LMP or ultrasound, and both LMP and ultrasound (when GA by ultrasound is within 1 week of the GA estimated by the date of the LMP) [19]. We will also determine the predictive accuracy using the area under a receiver operator curve, based on predicted probability estimates obtained from logistic regression. We will determine from the data the optimal cutoff for the dichotomization of the T-SGAS using tree analysis. For this analysis, each of the four aforementioned reference standards will be separately considered as dependent variables and the birth weight and the T-SGAS as independent variables.

Secondly, we will use latent class analyses [20-23] to predict a preterm birth when neither the GA based on the date of the LMP nor GA based on the ultrasound are treated as a reference standard. Finally, we will conduct classification and regression tree (CART) analyses to identify specific items from the T-SGAS and combine them with birth weight to achieve an improved prediction of a preterm birth, since birth weights are universally measured in health facilities soon after birth. The CART analyses will also provide an optimum protocol for implementation of the T-SGAS in community settings, since birth weights are now universally measured in the health facilities soon after birth. Improvement in discrimination and reclassification using the T-SGAS over the traditional method that uses birth weight and LMP will be quantified using the integrated discrimination improvement index and the net reclassification index, respectively [24,25].

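### Table 1 has no row for a total score of exactly 14, so its term band does not match the stated cutoff of <14 for preterm

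*Protocol article*

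**What the plan says.** The Introduction reports from the pilot work that "a score of <14 predicted that a newborn was preterm (GA of <37 weeks". The Methods section on development of the app adopts the same cutoff: "A score of <14 is considered to represent preterm, as we had found in our prior study". Neither place states a term threshold; term is whatever is not below 14.

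The same Methods section then points to the table: "The conversion of T-SGAS to GA categories is shown in Table 1". Table 1 gives four bands:

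| Total score | Gestational age (weeks) |
|---|---|
| <7 | <32 |
| 7-9 | ≥32 to <35 |
| 10-13 | ≥35 to <37 |
| >14 | ≥37 |

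The classification is automatic. Under Implementation of the Study Protocol: "The GA score is then auto-calculated and the neonate is classified into a specific GA group". The Analysis plan begins by using the Fleiss kappa to "estimate agreement between GA (as a dichotomous outcome) measured by ANM-1 and ANM-2". It then takes sensitivity and specificity for both nurse midwives against four reference standards.

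**The concern.** The last preterm band of Table 1 stops at 13 and the term band starts above 14. For whole-number scores this leaves 14 without a gestational age class, although the rule in the text puts it on the term side. The table and the text describe the same automated step, and they part exactly at the preterm/term boundary, which is the decision threshold of the test being validated.

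If the table was programmed as printed, a newborn scoring 14 would come out with no class. Such newborns would then be missing from the dichotomous comparison of the two raters and from the two-by-two tables at the pre-set cut. They would not be missing at random, since they all lie at the threshold. A reader who applies the published table by hand would meet the same gap.

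**Working it through.** **1. Range of the total.** The Introduction gives the item ranges: "posture (0 to 4), skin (–1 to 5), breasts (–1 to 4), and genitals (–1 to 4".
- Minimum: 0 + (-1) + (-1) + (-1) = -3.
- Maximum: 4 + 5 + 4 + 4 = 17.
- Item combinations: 5 × 7 × 6 × 6 = 1260.

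**2. Is 14 attainable?** A total of 14 is 3 points below the maximum. The 3 points can be taken from four items in C(6,3) = 20 ways. Every item can lose at least 3 points, so all 20 are valid. Hence 20 of the 1260 combinations give 14. This shows only that the score can occur; it is not a frequency among newborns.

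**3. Table 1 applied as printed to each total from -3 to 17.**

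| Total | Table 1 | Rule in the text (<14 preterm) |
|---|---|---|
| -3 to 6 | <32 weeks | preterm |
| 7 to 9 | ≥32 to <35 weeks | preterm |
| 10 to 13 | ≥35 to <37 weeks | preterm |
| 14 | no row | term, by complement |
| 15 to 17 | ≥37 weeks | term |

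Exactly one attainable total, 14, has no class in Table 1. The two sources agree on every other total.

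**4. What restores consistency.** If the last row is read as ≥14, every total from -3 to 17 has exactly one class and none conflicts with the <14 rule.

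**5. Direction of the effect if scores of 14 are dropped as unclassified.** Let Se and Sp be the values under the <14 rule, s the share of preterm newborns scoring 14, and t the share of term newborns scoring 14. Under the <14 rule the former are false negatives and the latter true negatives. Dropping both gives:
- Se′ = Se / (1 − s), which is not below Se;
- Sp′ = (Sp − t) / (1 − t), which is not above Sp.

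Kappa would lose every pair in which either rater gave 14. Under the <14 rule a 13/14 pair is a disagreement and a 14/15 pair an agreement, so the direction for kappa is not determined. The article gives neither s nor t, so no size can be computed.

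**6. Sample size.** The stated calculation ("a sample size of 7440 will achieve 80% power at a significance level of 0.05") uses prevalence, sensitivity and specificity, not the score cut. A one-sample test of proportions, n = (1.96·√(p0(1−p0)) + 0.842·√(p1(1−p1)))² / (p1−p0)², gives:
- 0.60 against 0.65: 742 preterm newborns, and 742/0.10 = 7420, against 7440 stated;
- 0.70 against 0.75: 638 term newborns, and 638/0.90 = 709, against 704 stated.

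Both stated figures are reproduced to within 3%, and the gap in Table 1 does not touch them.

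**The case against.** The strongest reply is that this is a typographical slip. The Introduction, the Methods text and the upper preterm band of Table 1 (ending at 13) all express one rule for whole-number scores, and all cite the same earlier study. Only the term row is out of line, and one changed symbol repairs it. For the dichotomous outcome the text already gives a complete rule: below 14 or not. The article also says that the app was tested frequently during development, and nothing shows that it left a 14 unclassified.

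Most of this stands. It is a reason not to read the table as a second, competing rule that makes 14 preterm. A reader might infer that term newborns scoring 14 become false positives, and that specificity falls by the share of term newborns with that score. No passage classes 14 as preterm, so that inference has no support. Any percentage attached to it would only restate an assumed share.

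Nor does every accuracy result depend on the point. The AUC, the cutoff found by tree analysis and the CART on individual items do not rest on the fixed cut.

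The reply does not remove the gap. Loss of a symbol when the text was extracted is unlikely, because ≥ is preserved in the same row of the table. The article names Table 1 as the conversion and nowhere says how a 14 is handled.

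**Conclusion.** The point holds as an internal inconsistency at the decision threshold. Table 1 omits the attainable total of 14, and its term band (15 to 17) does not match the term side of the stated cutoff (14 to 17).

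The consequence is conditional. If the app or the analysis dataset follows Table 1 literally, newborns scoring 14 are unclassified, and the kappa and the sensitivity and specificity at the pre-set cut are affected. If the app follows the text, the classifications are sound and only the printed row is wrong. The documents do not settle which applies. The conclusion assumes whole-number item scores, as the picture scale implies. The size of any effect is unknown.

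**What to change.** - Reconcile the last row of Table 1 with the <14 rule in the Introduction and Methods, so that every total has one class and the table and text agree.
- Confirm from the app's specification or code which rule it applied to a total of 14.
- If that rule differs from the reconciled one, re-derive the class from the stored item scores on forms SGAS01 and SGAS02 for every assessment totalling 14. Do this before computing kappa, sensitivity and specificity at the pre-set cut, and report how many assessments were involved.

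The cost is one table row, one check of the app and, if needed, one recomputation. Enrollment has ended and no new data are required.
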